**Methods/design:**

EMPOWER is a multicenter, double masked, randomized controlled phase-II trial to evaluate the safety and effectiveness of domperidone in those mothers identified as having difficulty in breast milk production. Eligible mothers will be randomized to one of two allocated groups: **Group A**: domperidone 10 mg orally three times daily for 28 days; and **Group B**: identical placebo 10 mg orally three times daily for 14 days followed by domperidone 10 mg orally three times daily for 14 days. The primary outcome will be determined at the completion of the **first 2-week period**; the second 2-week period will facilitate answering the secondary questions regarding timing and duration of treatment. To detect an estimated 30% change between the two groups (from 40% to 28%, corresponding to an odds ratio of 0.6), a total sample size of 488 mothers would be required at 80% power and alpha = 0.05. To account for a 15% dropout, this number is increased to 560 (280 per group). The duration of the trial is expected to be 36–40 months.

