## Methods/design

### Primary research question

The primary research question is: in mothers of preterm infants 23–29 completed weeks (23 1/7-29 6/7 weeks) gestation at birth who are pumping to provide expressed breast milk for their infant(s) and are identified as having an inadequate milk supply, does the administration of domperidone compare to placebo increase breast milk volume without any signs of harm over a 2 week period?

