### Secondary research questions

There are several secondary research questions:

i. Is there a relationship between the volume of breast milk produced and timing of initiation and duration of domperidone to treat mothers with defined low breast milk supply?

ii. Does gestation at birth contribute to any treatment effect from domperidone in mothers with defined low breast milk supply?

iii. Is there a difference in the volume of breast milk produced in mothers identified having an inadequate supply within 7–14 days post delivery versus mothers identified 15–21 days post delivery?

iv. Is there a difference in the use of supplementation such as donor breast milk or preterm infant formula between the different strategies of administration during the study period?

v. Is there a difference in the use of supplementation, such as formula or donor breast milk by the mother to her infant at 40 weeks post conceptual age (term) and at 6 weeks corrected age (6 weeks post term) between the two groups?

vi. Is there a difference in potential adverse events or effects, in particular, those related to gastrointestinal or cardiac difficulties between the two approaches?

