### Randomization

Upon consent, the site co-ordinator will be able to randomize the mother using a 24 hour/day web-based randomization service at the data coordinating centre (DCC) at the Centre for Mother, Infant, and Child Research (CMICR) in Toronto. A treatment number will be issued which will correspond to the study medication at the centre which has been previously sent to the site. The study allocation will be randomly assigned in a 1:1 ratio in blocks of 4 and 8. The study participants will be stratified by centre, gestational age groupings (23–26 and 27–29 weeks gestation at delivery) and days post delivery (7–14 and 15–21 days post delivery).

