### Statistical analysis

All analyses will be carried out using SAS Version 9.1 (SAS Institute, Cary, NC, USA). Descriptive statistics will be calculated for all variables of interest. Continuous measures will be summarized using means and standard deviations whereas categorical measures will be summarized using counts and percentages.

The primary outcome will be assessed between groups using a logistic regression model. This model will account for correlation among observations taken at the same centre as well as multiple births by the same mother using generalized estimating equations. The model will take into account variables such as gestational age and days post delivery. The number of variables included in the model will be determined using regression modeling guidelines (i.e. for logistic models, the maximum number of variables allowed will equal the number of observations in the smallest of the two outcome categories divided by 10). Prior to analysis, variables will be assessed for the presence of multi-collinearity (tolerance statistic < 0.4), and in this case, only one member of a correlated set will be retained in the model.

The secondary outcomes involving mean difference in the tabulated volume in breast milk will be assessed using a repeated measure analysis of covariance comparing the different groups across the time points of interest, adjusting for correlation among observations taken at the same centre and on the same subject. The model will assess differences between groups, differences over time (within-subject differences), and the group by time interaction adjusting for gestational age and days post delivery.

A linear regression model will be run to assess the relationship between gestational ages at time of delivery on the volume of milk. The model will include group, gestational age (23–26 weeks, or 27–29 weeks), as well as the group by age interaction term. Another linear regression model will be run to assess the relationship between timing of inadequate milk supply post delivery on the volume of milk. The model will include group, timing (7–14 days, 15–21 days), as well as the group by timing interaction term. All regression models conducted in this study will be run using likelihood based methods to account for missing data. The models will also treat twins or triplets as a correlated set of data to adjust for their dependent nature.

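### Secondary question ii on gestation is tested with a single cut at 27 weeks, and the gestation and timing interaction models each leave out the other moderator

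*Protocol article*

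**What the plan says.** The protocol article's Secondary research questions ask, as item ii, "Does gestation at birth contribute to any treatment effect from domperidone". The question is put without bands. The Primary research question defines the population as "23–29 completed weeks (23 1/7-29 6/7 weeks) gestation at birth", and the inclusion criteria repeat that range, so gestation is available to the day. Entry is allowed from postpartum day 7 to day 21.

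The Statistical analysis section then fixes two linear regressions of milk volume. For gestation: "The model will include group, gestational age (23–26 weeks, or 27–29 weeks), as well as the group by age interaction term". For timing: "Another linear regression model will be run to assess the relationship between timing of inadequate milk supply", with group, two timing bands (7–14 and 15–21 days) and their interaction. Neither model contains the other moderator. The article does not say which day's volume these models use.

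The same bands are the randomisation strata (Randomization) and appear in secondary outcomes iii and iv. Question iii, unlike question ii, is itself worded as the earlier band against the later one.

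**The concern.** There are two separate issues.

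First, a two-level factor treats 26 6/7 and 27 0/7 weeks as different and 23 1/7 and 26 6/7 weeks as the same. If the treatment effect changes gradually with gestation, this discards information that has already been collected. The trial is sized for its primary comparison and states no power for any interaction, so there is little to spare.

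Second, with the moderators in separate models, an effect that varies with gestation can show up in the timing model whenever gestation and entry day are related. Some relation is conceivable: inadequate supply is judged against 150 ml/kg/d, so the volume required depends on infant weight, which varies with gestation. The protocol gives neither the size nor the direction of any such relation.

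At stake are the answers to questions ii and iii: a gestation trend that is missed, or a timing difference read as due to timing when part of it is gestation.

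**Working it through.** **The plan's own figure.** The abstract gives "To detect an estimated 30% change between the two groups (from 40% to 28%, corresponding to an odds ratio of 0.6" and "a total sample size of 488 mothers would be required at 80% power and alpha = 0.05". With 1:1 allocation, two-sided alpha 0.05 and pooled variance, n per arm = [1.960 × √(2 × 0.34 × 0.66) + 0.842 × √(0.40 × 0.60 + 0.28 × 0.72)]² / 0.12² = (1.313 + 0.559)² / 0.0144 ≈ 243.4, so 244 per arm and 488 in total. The figure reproduces. It concerns the primary comparison only.

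**Information kept by the gestation cut.** From 23 1/7 to 29 6/7 there are 48 possible days, 27 below 27 0/7 and 21 at or above it. With a uniform distribution (assumption) the band means are 24 days apart and the variance is (48² − 1)/12 = 191.9. The squared correlation of band with exact gestation is (27/48) × (21/48) × 24² / 191.9 = 141.75 / 191.9 = 0.739. If frequency rises two- to eight-fold across the range, it is 0.743 to 0.725.

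**Power under a gradual (linear) trend.** Power = Φ[(1.960 + 0.842) × √r² − 1.960]. With r² = 0.739 this is Φ(2.408 − 1.960) = Φ(0.448) = 67%. The range 0.725 to 0.743 gives 66% to 68%. Recovering 80% would need 1/0.739 = 1.35 times the sample.

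**Power under a step at 27 weeks.** The same formula applies with the roles reversed. By simulation, a step of equal variance is found in about 79% of trials with the bands and about 67% with continuous gestation.

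**Separate timing model.** I simulated 10,000 trials of 488 mothers with uniform margins, a set correlation on the underlying normal scale, a linear gestation interaction and no timing interaction. The large interaction is 2.802 / (0.5 × √488) = 0.254 residual SD per SD of gestation, chosen to give 80% power for the continuous test (79% in simulation, against 66% with the bands). The joint model has group by continuous gestation and group by timing band. The table shows how often the banded timing interaction is rejected.

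| Correlation | Alone, large interaction | Alone, half interaction | Joint, large interaction |
|---|---|---|---|
| 0 | 4.7% | 4.8% | 4.8% |
| 0.1 | 5.3% | 5.1% | 4.9% |
| 0.2 | 7.1% | 5.6% | 5.1% |
| 0.3 | 9.8% | 6.3% | 5.2% |
| 0.5 | 19.2% | 8.5% | 4.9% |

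Half the interaction has about 28% power on continuous gestation. In the joint model, power for the large gestation trend is 77% at correlation 0.3 and 73% at 0.5. That is below the 79% from fitting continuous gestation alone, and above the 66% of the planned banded model.

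**The case against.** The bands are prespecified, match the strata and appear in outcomes iii and iv, so there is no data-driven cut point. No passage contradicts another and no stated figure is wrong. All of that stands. It justifies the bands for randomisation and display. It does not require them for the test of question ii, which asks about gestation without bands.

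Four stronger readings are tempting, and the document does not support them.

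- A reader might infer that the timing bands are equally a fault. Question iii and outcome iv are stated as days 7–14 against days 15–21, so the banded contrast is the question asked. A slope on entry day would answer a different one.
- A reader might infer that banding always costs power. The loss belongs to a gradual trend and reverses with a step at the cut. The protocol gives no shape.
- A reader might infer that the separate timing model inflates false positives outright. If gestation and timing are correlated and the effect varies with gestation, the effect does differ between early and late entrants, and the separate model reports that marginal difference correctly. It is an error only if the result is read as timing acting independently of gestation. Its size also needs a sizeable correlation and a large gestation interaction.
- A reader might infer that the trial's guidance on when to treat rests on these models. The Design section assigns timing and duration of treatment to the second two-week period, so neither subgroup model is its main source.

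**Conclusion.** The concern holds for the test of question ii. A single cut at 27 weeks keeps about 74% of the information on a gradual trend, so 80% power falls to about 67%. This rests on a roughly linear change across gestation and on a uniform or moderately rising distribution. Under a step at 27 weeks the banded test is the better one.

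The omission of each moderator from the other's model is a risk to interpretation, not a demonstrated error. It is negligible at a correlation of 0.1 or less. With a large gestation interaction the timing test rejects in about 10% of trials at 0.3 and about 20% at 0.5; with half that interaction it stays near 5 to 6% up to 0.3. The correlation and the interaction size are both assumptions.

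Only secondary outcomes iii and iv are touched. The primary analysis and the 488 and 560 totals are unaffected.

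**What to change.** Fit one model for day-14 volume, the end of the placebo-controlled period, with group, gestation in weeks and days, timing band (7–14 or 15–21 days), group by gestation and group by timing band.

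- Test question ii by the group-by-gestation term, linear, with a spline or the banded estimates as a check on shape.
- Test question iii by the group-by-timing-band term, which keeps the stated contrast and adjusts it for gestation.
- Report treatment effects by gestation band and timing band as the descriptive display by stratum.

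The change is to analysis wording only; the data are already needed for eligibility and stratification. The costs are a shape assumption for gestation, with lower power than the bands if the effect really steps at 27 weeks, and slightly wider intervals in the joint model when the moderators are correlated.

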## Discussion

Currently, there is no clear approach in managing mothers of preterm infants experiencing an inadequate production of breast milk. With EMPOWER, we hypothesize that domperidone, through its pharmacologic action on increasing prolactin levels, will assist mothers of very preterm infants, experiencing inadequate breast milk production, in increasing breast milk volumes to a level identified as being sufficient for continued pumping in the hospitalization period. We also hope to determine the safety and efficacy of domperidone in helping a mother who is experiencing an inadequate milk supply, and how it should be considered in the care of the mother and her preterm infant without causing adverse consequences to either the mother or infant.

